### 2.3. Assessment

The primary end point will be the difference in pain intensity, assessed on a 100-point visual analogue scale (VAS), between the educated OLP and the deceptive placebo treatments at the end of the placebo condition CPT. We have chosen pain intensity as opposed to pain threshold because it involves less motivational and cognitive components [33].

The main secondary end point will be, for each subject, the difference in pain intensity, also assessed by VAS, between open or deceptive placebo versus no-treatment control. Secondarily, a questionnaire (inspired by Hughes et al.’s data [34]) measuring knowledge regarding the placebo effect will be completed by all the subjects after the study and also before the educational video for the educated placebo group. In addition, all the subjects will complete another questionnaire about their perception of the investigators and of the study [35]. Blood pressure (BP) and heart rate (HR) values will be obtained before, during, and after each CPT by means of an automatic blood pressure monitor. Finally, subject’s anxiety will be evaluated through heart rate variability. Before the CPT treatment, an expectancy questionnaire will be used [36].

We expect to find a non-inferiority between both groups on the main end point. Considering the nature of the dependent variables and the choice of the painful stimulation, we expect a high interindividual variability. This has been limited as best as possible by the cross-over conducted in both arms of the study.

### 2.4. Subjects

Participants are to be recruited via advertisements for a study of a painkiller cream, on the Grenoble University campus. Inclusion criteria are: being aged between 18 and 40 years old, registered to the national healthcare, having understood and signed the written consent. Non-inclusion criteria were the following: legal impossibility to participate to the protocol (i.e., pregnant women, people deprived of their liberty) or affections modifying the painful stimulus used (any known pathology affecting the venous, arterial, or lymphatic system, diabetes, cardiac affections, asthma, frostbite on the hand, epilepsy, hand arthritis, lupus erythematosus, and allergic reactions to the cream, under pain regulation medication).

All medication that could impact pain sensation, such as painkillers or psychotropics, have to be stopped three weeks prior to experiment, as will alcohol in the 24 h prior to the experiment.

Socio-demographic information will be collected in order to control the impact of these variables in the representation of the placebo effect and consequently expectations towards the treatments.

### 2.5. Ethical Considerations Regarding the Study Protocol

During conceptualization of the protocol, several ethical questions were raised. The first was about the information given while administering the cream as a deceptive placebo. While it was first considered to present it as “an analgesic cream”, this was deemed too much of a deception and unethical. The committee in charge of ethics agreed on the use of the sentence “This is a cream useful for treating pain” as it was argued that was true due to its non-specific effect.

Secondly, the choice of reaching 7/10 as a threshold on the VAS was debated. It was argued that this was a high level of pain. However, the duration of this intense pain was deemed short enough to present little risks and be a probable situation in a clinical setting. The treatments used in the case of pain rated over 7/10 are also those with the most side-effects and thus these types of intense pain experiences would benefit most from OLP treatments. The time frame required to obtain a score of 7 on the VAS with a CPT is still within a reasonable duration.

Lastly, among the often-used pain stimulation methods, the choice of using a CPT was also questioned. This point is discussed in the discussion below.

### 2.6. Material

The Cold Pressor Test (CPT), Dip Cooler RU 200 from Techne^®^ (Cole Parmer, Staffordshire, United-Kingdom) will deliver the pain stimulus. The duration of the immersion will be calibrated during the first CPT and maintained for an identical time in the two others. More on the use of the CPT is presented below.

Tablets will be used to fill out the assessments as well as watch the videos. The content of the educational video will be detailed below. The control video (about the history of hygiene and Semmelweis) was taken from a well-known video broadcasting website with written consent from the creator.

The placebo treatment used for both groups is a neutral cream with no active pharmacological substance: CremaFluid Phytomedica^®^ (Laboratoires Phytomedica, Aix-en-Provence France). It will be presented as a placebo cream in group 1 (educated placebo) and as a painkiller in group 2 (deceptive placebo).

### 2.7. Randomization

Randomization was carried out in several steps. Firstly, an analyst from inside the team wrote the code to get a randomized spreadsheet of groups and CPT orders. The rest of the procedure was conducted by the research team’s staff not involved in the protocol. Another analyst was asked to attribute to each group an unidentifiable name in order to blind the analysis of results (group A and group B) as well as choose a random seed. Lastly, another person made individual, numbered, and sealed envelopes with the randomization results inside. This entire process was done with no involvement from the investigators. The envelopes are kept under lock and key.

This process allows for preservation of the blinding of the analyst (not knowing which treatment group A and B received) and maintains the investigator in the dark regarding group attribution until the envelope is opened.

### 2.8. CPT Procedure

Each volunteer will be initially subjected to a calibration test according to the CPT procedure and then to the experimental tests. After this, a debriefing and two questionnaires will conclude the inclusion.

Each CPT procedure is as follows. Every CPT is preceded by a 3 min monitored resting period where heart rate and respiratory rate are measured. Blood pressure is measured at the end of this 3 min baseline assessment. The hand and forearm temperature will be checked on both sides for reference. The non-dominant hand and distal third of the forearm will be immerged into the CPT at 1 °C +/− 1 °C. The forearm length submerged in the cold-water tank will be determined as follows: 1/3 of the distance between the ulnar styloid and the tip of the olecranon. The elbow will be placed on the outer rim of the water tank and the hand relaxed with no contact with the bottom of the tank.

For the calibration CPT, patients will be asked to record the intensity of their pain on the VAS every 5 s approximately. When the intensity exceeds 7/10 on the VAS, the subject will be told to remove his or her hand from the water. The time at which this event occurs will be referenced as (*t*). For both of the other CPTs, patients will be asked to keep the hand in the tank during (*t*) seconds and complete a VAS as soon as the hand is taken out of the water.

In between each CPT, a 20 min pause is mandatory and skin temperature is checked before the next CPT. If needed, a tank of warm water at approximately 25 °C can be used to warm up the hand until it reaches contralateral temperature.

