### 2.9. Part I: Calibration

The protocol can be described in three different phases described below. The first phase is the calibration. Subjects are greeted by the main investigator who will explain in detail the nature of the pain stimulation applied and inform subjects of their rights regarding data privacy and protocol interruption. Inclusion and non-inclusion criteria are checked before signing a written consent. Once consent is obtained, the randomization envelope is opened to allocate subjects to a group and determine the order of the CPTs. The calibration CPT can then start following the procedure stated above in part 2.8.

This calibration will enable us to use a constant duration for the immersion of the hand in the water for the two remaining CPTs, and will allow us to ensure that the intensity of pain is homogeneous.

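### The randomisation envelope is opened before calibration has shown whether the immersion time t exists, so a subject who yields no t is already in the ITT set

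*Protocol article*

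**What the plan says.** All references are to the Protocol article.

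- **Section 2.8 (CPT Procedure).** During calibration the subject rates pain about every 5 s. "When the intensity exceeds 7/10 on the VAS, the subject will be told to remove his or her hand from the water". The time of that event is t, and no other definition of t is given. For the other two CPTs, "patients will be asked to keep the hand in the tank during (*t*) seconds", and a VAS is completed as the hand comes out.
- **Section 2.3 (Assessment).** The primary VAS is the one at the end of the placebo-condition CPT, that is, after t seconds.
- **Section 2.9 (Calibration).** "Once consent is obtained, the randomization envelope is opened to allocate subjects to a group and determine the order of the CPTs". The next sentence reads: "The calibration CPT can then start following the procedure stated above in part 2.8". The section adds that calibration "will allow us to ensure that the intensity of pain is homogeneous".
- **Section 2.4 (Subjects).** "Inclusion criteria are: being aged between 18 and 40 years old, registered to the national healthcare, having understood and signed the written consent". Neither this list nor the non-inclusion list refers to the calibration result.
- **Section 2.2 (Design).** Investigators are not blind.
- **Section 2.13 (Statistical Analysis).** All participants are analysed in the group to which they were randomised. A per-protocol analysis is added.
- **Duration.** Section 2.5 says: "The time frame required to obtain a score of 7 on the VAS with a CPT is still within a reasonable duration". Section 4.1 gives an average of 40 s to pain tolerance at 1 °C.

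**The concern.** Whether t exists is known only at the end of calibration, yet the subject is allocated before calibration begins. Every later measurement depends on t: the placebo CPT (primary outcome), the control CPT (a covariate in the primary regression) and the within-subject contrast between them (main secondary endpoint). If pain levels off at or below 7/10, or the hand comes out early, the subject is in the ITT set with no defined duration for either experimental CPT.

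Two things can then happen. The subject may contribute no usable primary value, which costs power. Or an investigator who has seen the allocation may choose a duration on the spot. The value then exists, but it was obtained at a pain level that the calibration did not set. Either way the homogeneity that section 2.9 expects from calibration is not achieved for that subject. Sections 2.3 and 4.1 both expect high variability between subjects, so the case is foreseeable.

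**Working it through.** **1. Order of events, sections 2.8 to 2.10 side by side**

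| Step | Section | Is t known? | Is the arm known to the investigator? |
|---|---|---|---|
| Consent | 2.9 | no | no |
| Envelope opened | 2.9 | no | yes |
| Calibration CPT | 2.8, 2.9 | only if VAS exceeds 7/10 | yes |
| Group-specific video in the pause | 2.10 | as above | yes |
| Two experimental CPTs of t seconds | 2.8, 2.10 | required | yes |

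The allocation is first needed at the pause after calibration, when the group-specific material is given. Nothing before that step uses it.

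**2. The plan's own sample size**

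Inputs: margin 10 mm, SD 21.9 mm, alpha 0.05, power 80% (section 2.12); one-sided 95% interval (section 2.13); true difference taken as 0.

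n per group = 2 × (1.645 + 0.842)² × 21.9² / 10² ≈ 59.3, rounded up to 60. This matches the stated figure. Then 120 × 1.05 = 126, which also matches. There is no arithmetic error in the plan. The allowance is 126 − 120 = 6 subjects for all causes of unusable data together.

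**3. Power if subjects without a t are unusable**

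The share f of such subjects is not in the article; the values below are assumptions. With 63 × (1 − f) per group, SE = 21.9 × √(2/n) and power = Φ(10/SE − 1.645).

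| f (assumed) | Subjects of 126 | n per group | SE (mm) | Power |
|---|---|---|---|---|
| 0% | 0 | 63.0 | 3.90 | 82.1% |
| 5% | about 6 | 59.85 | 4.00 | 80.3% |
| 10% | about 13 | 56.7 | 4.11 | 78.4% |
| 20% | about 25 | 50.4 | 4.36 | 74.1% |

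If other causes also remove 5%, the same rows become 80.3%, 78.5%, 76.6% and 72.2%.

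Under the present order, keeping 120 evaluable subjects needs 120/(1 − f) randomised: 127, 134 or 150 at 5%, 10% or 20%.

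These figures use the plan's unadjusted SD. The primary regression adjusts for pain without placebo, which may reduce the residual SD, so actual power could be higher.

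**The case against.** **The article is condensed.** A maximum immersion time, or a rule for subjects who do not reach 7/10, may stand in the full protocol. This holds, and the absence of a printed limit is not counted as an error here. It does not answer the point about order, because section 2.9 states that order outright.

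**A reader might infer unlimited cold exposure, or a contradiction with section 2.5.** The text does not support either. Section 2.9 tells subjects of their right to interrupt. Section 2.5 speaks of the usual time to reach 7, and section 4.1 of an average. Silence about an unusual subject contradicts neither. What stands is narrower: the article prints no procedural end for a subject who stays at or below 7/10, and interrupting the test does not yield t.

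**A reader might infer that no primary endpoint can exist for such a subject.** That goes too far. A VAS can be taken after any fixed duration, and the regression adjusts for the subject's pain without placebo. If the value is missing, section 2.13 has a missing-data rule and section 2.12 a 5% allowance. But the text does not assign these subjects to that rule. If a duration is improvised, nothing is missing and the rule is not triggered. If no t is set at all, the control-CPT covariate is lost as well. Nor does the article say whether an improvised t counts as a protocol deviation for the per-protocol set.

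**A reader might infer a bias towards non-inferiority**, since subjects with little pain dilute the contrast between arms. This would require such subjects to be analysed and to show little arm difference, which is not established. It is also an alternative to the power loss: the same subject cannot be both lost and diluting. Section 4.2 further requires both placebos to beat no treatment before a clinically relevant conclusion, and low pain throughout would make that harder. Calibration precedes the group-specific video, so the arms should not differ in the share of such subjects through the intervention itself.

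**The size may be small.** This is fair. At 5% the planned power is kept, and the pre-testing reported in section 3 mentions no failure to reach 7/10.

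**Conclusion.** The point holds as a fault in the order of steps. Allocation precedes the only step that can show whether t exists, and ITT keeps the subject in the analysis. Any handling is left to investigators who already know the arm.

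The size depends on a share that the article does not give. At an assumed 5% the planned 80% power is retained; at 10% to 20% it falls to about 78% to 74%. This assumes that the subjects are unusable, that the SD is 21.9 mm and that the true difference is 0. No bias in a given direction is shown, and no safety breach is claimed.

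This is a should-fix, not a must-fix: the effect may be small, but the rule is explicit and cheap to change.

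**What to change.** - **Section 2.9.** Open the envelope only after calibration has produced t. Record subjects without a t as not randomised and replace them. Their envelope stays sealed for the next subject, so the numbered sequence is kept. Section 2.10 needs the allocation only from the pause onwards, so the session does not change otherwise.
- **Subjects already randomised** (recruitment began in May 2019, section 3). Flag those who did not exceed 7/10 and report the primary analysis with and without them. The ITT analysis should keep them. The analysis without them is a sensitivity check, because their calibration was run by investigators who knew the arm.
- **End of immersion.** The sponsor and ethics committee should reconcile section 2.8 with sections 2.5 and 4.1 and with any limit in the full protocol. No limit is proposed here.

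The cost is a short amendment and some extra calibration sessions. To randomise 126 subjects, 126/(1 − f) must be calibrated: 133, 140 or 158 at an assumed 5%, 10% or 20%, which is 7, 14 or 32 extra sessions that end at calibration. The population becomes limited to subjects who exceed 7/10, which is the pain level that section 4.1 says the work is aimed at.

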### 2.9. Part I: Calibration

The protocol can be described in three different phases described below. The first phase is the calibration. Subjects are greeted by the main investigator who will explain in detail the nature of the pain stimulation applied and inform subjects of their rights regarding data privacy and protocol interruption. Inclusion and non-inclusion criteria are checked before signing a written consent. Once consent is obtained, the randomization envelope is opened to allocate subjects to a group and determine the order of the CPTs. The calibration CPT can then start following the procedure stated above in part 2.8.

This calibration will enable us to use a constant duration for the immersion of the hand in the water for the two remaining CPTs, and will allow us to ensure that the intensity of pain is homogeneous.

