### 2.2. Design

We will conduct a non-inferiority randomized, parallel with a nested crossover trial comparing educated open-label placebo to deceptive placebo. This monocentric study will be carried out by two licensed physiotherapists in a University Hospital near the campus.

Written informed consent will be obtained from subjects prior to their participation in the study. The investigation will consist of a single two-hour session. Participants will receive a 20€ participation compensation.

The subjects meeting the inclusion criteria (detailed below) will be randomized into two groups: (1) educated placebo or (2) conventional/deceptive placebo. Each will be subjected first to a calibration CPT, and then, in a randomized order, will receive the CPT under the condition of interest (either the Conventional placebo CPT (CPTp) or the Educated placebo CPT (CPTe)) and a Control CPT (CPTc). This is represented in Figure 1.

Regarding blinding, investigators will not be blind as they deliver the treatment openly in the educated group. Patients in the deceptive placebo group will be blinded. However, patients in the educated placebo group will not be due to the nature of OLP. The analysis will be done blindly as the analyst will not know which group received which treatment.

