### 2.10. Part II: Experimental CPTs

During the break between calibration and the second CPT, the subject will receive the information related to the group they are randomized into. For the deceptive placebo group, the video will describe the history of hygiene and correct method for washing hands. For the educated placebo group, the video will be an educational video about placebo, its physiology, and the use of OLP. Movies are similar in terms of duration (~11 min), image quality, and format. After both videos, there will be a time where questions can be answered by the investigators. The educated placebo group will fill out a questionnaire regarding their knowledge of the placebo effect before watching the educational video.

The test phase will be divided into two parts in a random sequence to compensate for habituation effect: deceptive placebo CPT (CPTp) or educated placebo (CPTe) and control CPT (CPTc). For the CPTp and CPTe, two milliliters of the neutral placebo cream are applied beforehand following a standardized procedure: four round-trips on the forearm along its submerged part and on the dorsal and palmar side of the hand and an expectancy questionnaire is filled out. The immersion time (t) in cold water will be that previously calibrated.

While applying the neutral cream, the examiner will explain to the deceptive placebo group, that “it is a cream effective in fighting cold-related pain.” In the Educated placebo condition, the examiner states that it is “a placebo cream, containing no active substance that is effective in fighting cold-related pain. All the mechanisms shown in the previous film will be at work. In a way, your brain will be secreting the active components itself.”

Under the control condition, no cream will be applied.

The examiner will be aware that the same placebo cream is used for the two groups, in order to simulate real situations in which the practitioner administering or prescribing the placebo does so with full knowledge of its presence. The patient will not be blinded in the OLP group and will be blinded in the deceptive placebo group. The analyst will be blinded to group allocation.

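### The envelope is opened before the calibration CPT, so the immersion time used for the primary endpoint is obtained by an investigator who already knows the arm: an avoidable risk of bias, of unknown direction

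*Protocol article*

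**What the plan says.** Section 2.9 gives the order of events. After the consent step, "Once consent is obtained, the randomization envelope is opened to allocate subjects to a group and determine the order of the CPTs". Only then: "The calibration CPT can then start following the procedure stated above in part 2.8".

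Section 2.7 says that the procedure "maintains the investigator in the dark regarding group attribution until the envelope is opened", so concealment from the investigator ends at that moment. Section 2.2 confirms that "investigators will not be blind as they deliver the treatment openly in the educated group".

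Section 2.8 describes calibration. Here "patients will be asked to record the intensity of their pain on the VAS every 5 s approximately", and "When the intensity exceeds 7/10 on the VAS, the subject will be told to remove his or her hand from the water". Withdrawal at that point defines t, which is then carried forward: "For both of the other CPTs, patients will be asked to keep the hand in the tank during (*t*) seconds".

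Section 2.10 places the first arm-specific step later: "During the break between calibration and the second CPT, the subject will receive the information related to the group they are randomized into". Section 2.3 defines the primary endpoint as the between-arm VAS difference at the end of the placebo-condition CPT. Section 2.13 analyses it by linear regression on control-CPT pain and CPT sequence, and does not name t as a covariate.

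**The concern.** The immersion time t is the dose of the painful stimulus. If it differs systematically between arms, the primary VAS scores differ for a reason unrelated to the placebo rationale. In a non-inferiority comparison, slightly shorter immersions in the educated arm would push towards a false positive, and slightly longer ones would cost power.

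The article's reason for unblinded investigators is that treatment is delivered openly. That reason does not extend to calibration, where no treatment is delivered. The CPT order, also in the envelope, matters only from the second CPT. So knowledge of the arm during calibration serves no purpose in the design.

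There is a smaller consequence. A subject who withdraws during calibration, or never exceeds 7/10, has already been randomised and may have no t, and hence no primary value in the intention-to-treat set.

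**Working it through.** **Step 1: sequence, read across the sections**

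| Event | Section | Arm known to investigator? | Arm-specific information given to subject? |
|---|---|---|---|
| Consent | 2.9 | No | No |
| Envelope opened | 2.9, 2.7 | Yes, from here | No |
| Calibration CPT, t recorded | 2.9, 2.8 | Yes | No |
| Break: pre-video questionnaire (educated arm), video | 2.10 | Yes | Yes, from here |
| Placebo and control CPTs, each for t seconds | 2.8, 2.10 | Yes | Yes |

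The arm is first needed in the fourth row but is disclosed in the second. Section 2.9 does not say who opens the envelope; sections 2.2 and 2.7 together imply that the investigator knows the group from then on.

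**Step 2: the plan's own figure**

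Inputs from section 2.12: margin 10 mm, SD 21.9 mm, alpha 0.05 (one-sided interval per section 2.13), power 80%.

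n per group = 2 × (1.645 + 0.842)² × 21.9² / 10² = 59.3, rounded up to 60. This matches the plan. Power at 60 per group is 80.4%. Then 120 × 1.05 = 126, also as stated. The point disputes neither figure.

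**Step 3: illustration of size**

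None of the following assumptions comes from the documents:
- VAS rises linearly to 70 mm over 40 s, that is 70/40 = 1.75 mm per second. Section 4.1 gives about 40 s, but to pain tolerance, not to 70/100.
- Immersion is on average 1 s shorter in the educated arm, a mean shift d = 1.75 mm. The same mean arises if one 5 s rating step (5 × 1.75 = 8.75 mm) is lost in one educated subject in five: 8.75/5 = 1.75 mm.
- The shift is equal in the placebo and control CPTs, which have equal SDs and correlation rho of 0.5 to 0.7.

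Unadjusted SE = 21.9 × √(2/60) = 4.00 mm.

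Under the planned adjustment for control-CPT pain, the regression slope equals rho. Therefore:
- residual bias = d × (1 − rho)
- SE = 4.00 × √(1 − rho²)
- type I error at the margin = Φ(bias/SE − 1.645)

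| rho | Residual bias (mm) | SE (mm) | bias/SE | Type I error |
|---|---|---|---|---|
| 0.5 | 0.875 | 3.46 | 0.253 | 8.2% |
| 0.7 | 0.525 | 2.86 | 0.184 | 7.2% |

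**Step 4: the opposite direction**

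The same shift against the educated arm, with a true difference of zero, lowers power = Φ((10 − bias)/SE − 1.645):
- at rho 0.5, from 89.3% to 83.9%
- at rho 0.7, from 96.8% to 95.3%

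**The case against.** The strongest reply is that the investigator does not choose t. The subject rates the pain, a fixed rule (above 7/10) triggers withdrawal, and the subject has received no arm-specific information. Stopping someone at 7 or below would be a protocol deviation, which the per-protocol analysis in section 2.13 would exclude if it were recorded. All of this stands, and it limits the room for influence. It does not close it: ratings are only approximately 5 s apart, and a slightly different rhythm, instruction or call to withdraw would break no rule.

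The planned covariate also counts. Control-CPT pain is measured at the same t, so part of any shift cancels. Section 4.2 further requires both placebos to beat no treatment before a clinically relevant non-inferiority is concluded. Those within-subject contrasts use one t and are little affected, and the figures above ignore that condition.

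Reordering also leaves the later unblinded steps in place, including delivery of the arm-specific statement and conduct of the primary CPT. Section 4.2 acknowledges that there is no independent assessor.

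Stronger readings that a reader might infer are not supported:
- **That the order favours the educated arm.** The direction and the size of any shift are unknown.
- **That type I error reaches about 11%.** That is Φ(1.75/4.00 − 1.645) for an unadjusted analysis, which the plan does not use.
- **That one rating step nearly uses up the margin.** The 8.75 mm is a shift in one subject; the 10 mm margin applies to a difference in means.
- **That allocation concealment fails.** The envelope is opened after consent, so concealment at enrolment is intact.
- **That calibration loses its value as a baseline.** No planned analysis uses calibration pain as a baseline; the covariate is control-CPT pain.
- **That calibration failures bias the comparison.** They occur before subjects receive arm-specific information, so subject-driven losses should not differ by arm. No rate is given, and sections 2.12 and 2.13 provide a 5% allowance and an imputation rule.

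**Conclusion.** The point holds as an avoidable risk of bias, not as evidence that bias occurred. The stated order lets an investigator who knows the arm run the step that yields the stimulus duration for the primary endpoint, although the design does not need the arm to be known then. The blinded analyst and the self-reported outcome, on which section 4.2 relies, cannot undo an exposure time already obtained with the arm known. The control-CPT covariate corrects it only in part.

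The size is modest: about 7-8% instead of 5% under an assumed 1.75 mm shift favouring the educated arm, or some loss of power if the shift goes the other way. These figures rest on the assumed linear rise, shift and correlations. The change is worth making because it costs little, but the risk does not by itself undermine the trial.

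**What to change.** In section 2.9, run the calibration CPT and record t first. Open the envelope at the start of the break, before the pre-video questionnaire and the video, and randomise only subjects with a recorded t. Section 2.7 can stay as it is.

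Section 3 reports that recruitment started in May 2019, so some subjects may already have been calibrated under the present order. Flag those enrolled before and after the change, report t by arm, and add a sensitivity analysis of the primary endpoint adjusted for t. That analysis is a check rather than a full correction: across subjects, t also reflects pain sensitivity, so its coefficient is not purely an effect of immersion time.

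The cost is a small procedural amendment during the trial and the before/after distinction it creates. It needs no extra subjects: 60 per group and 126 in total stand. The later unblinded steps remain and should still be reported as a limitation.
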